## Abstract

**Background:**

Children of parents with a mental illness or substance use disorder (COPMI) have an increased risk of developing social-emotional problems themselves. Fear of stigmatisation or unawareness of problems prevents children and parents from understanding each other. Little is known about COPMI with mild intellectual disabilities (ID), except that they have a high risk of developing social-emotional problems and require additional support. In this study, we introduce a program for this group, the effectiveness of which we will study using a quasi-experimental design based on matching. The program ‘You are okay’ consists of a support group for children and an online educational program for parents. The goal of the program is to increase children and parents’ perceived competence with an aim to prevent social-emotional problems in children.

**Methods/Design:**

Children between ten and twenty years old with mild ID (IQ between 50 and 85) and at least one of their parents with a mental illness will be included in the study. The children will receive part time treatment or residential care from an institute for children with mild ID and behavioural problems. Participants will be assigned to the intervention or the control group. The study has a quasi-experimental design. The children in the intervention group will join a support group, and their parents will be offered an online educational program. Children in the control group will receive care as usual, and their parents will have no extra offer. Assessments will be conducted at baseline, post-test, and follow up (6 months). Children, parents, and social workers will fill out the questionnaires.

**Discussion:**

The ‘You are okay’ program is expected to increase children and parents’ perceived competence, which can prevent (further) social-emotional problem development. Because the mental illness of parents can be related to the behavioural problems of their children, it is important that children and parents understand each other. When talking about the mental illness of parents becomes standard in children’s treatment, stigmatisation and the fear for stigmatisation can decrease.

**Trial registration:**

Dutch Trial Register NTR4845. Registered 9 October 2014.

**Electronic supplementary material:**

The online version of this article (doi:10.1186/s12888-015-0698-0) contains supplementary material, which is available to authorized users.

## Background

Research has shown that children of parents with a mental illness (COPMI) or substance use disorder are at risk of developing social-emotional problems themselves. In this study, COPMI refers to children of parents with a mental illness as well as children of parents with a substance use disorder. These children have a two to thirteen-fold higher risk of developing social-emotional or addiction problems compared to their peers with parents without a mental illness. Moreover, they also make more use of mental health care resources [1, 2].

The increased risk of COPMI can be explained by genetic, biological, and environmental factors surrounding children, their families, and their social network. Examples of genetic and biological factors include genetic predispositions and neurobiological processes during pregnancy [1, 2]. The important role of nurture and the environment in which a child grows up will form central risk factors in this study. For parents with a mental illness, it can be difficult to offer children enough regularity, safety, and positive attention. Parents can also have difficulties talking about their problems for a number of reasons. They can, for example, fear stigmatisation or be ashamed or unaware of having a mental illness, or they may not understand that their problems affect the behaviour of their children [3]. Other parents are afraid that their children might be placed out-of-home, and/or they do not want to burden their children with their problems. As a result, children and parents often do not understand each other. This can lead to these children developing feelings of guilt, shame, loneliness, and social isolation. Moreover, COPMI often show low levels of self-esteem and social acceptance [4–6].

Different preventive interventions, such as support groups, were developed for COPMI with average intelligence aimed at decreasing risk factors and improving protective factors. COPMI with mild ID are a high-risk group that has not been reached yet by preventive interventions [2]. Although little research has been conducted on COPMI with mild ID, four important risk and protective factors in both children and their parents may influence (further) social-emotional problem development. Most important risk factors are the presence of mild ID and behavioural problems in these children and the presence of a mental illness and mild ID in parents [7–9]. The combination of multiple risk factors is associated with higher risks of social-emotional problem development [2]. On the other hand, several important protective factors may prevent (further) social-emotional problem development. First, intrapersonal characteristics, such as perceived competence in both children and parents, serve as protective factors. Second, parent-child interactions, like positive parenting behaviour and parental involvement with their child’s treatment, are additional protective factors. Third, social support from children and parent’s social network can positively influence the prevention of social-emotional problems [2, 10].

Research showed that 66 % of children with mild ID and behavioural problems have a parent with a mental illness [7]. Despite these children’s increased risk and high prevalence, little research has been done on this specific group and no preventive interventions have been developed for them yet. More research is needed to test whether support groups developed for COPMI with average intelligence are effective in children with mild ID and their parents with a mental illness. COPMI with mild ID have particular needs, as described in Additional file 1 on which the ‘You are okay’-program will respond.

Over the years, various types of interventions for COPMI with average intelligence have been developed. The support group is the most common form, which is developed for children of different age groups. In these support groups, peers who have to cope with the same difficult situations come together to share experiences and feelings about coping with their parent with a mental illness. They get psycho-education to learn about their parents’ mental illness and to better understand their parent. In a safe context (small groups), they provide each other with support and practice new coping skills through, for example, role-playing games. Through stories of other children, they can learn that they are not the only ones with a parent with a mental illness and that the problems of the parent are not their fault.

The goal of these support groups is to increase protective factors and decrease risk factors. The aim is to empower the social network, take unrealistic thoughts away, increase perceived competence and strengthen the relationship between parent and child [10]. Research shows that these factors prevent (further) development of emotional and behavioural problems in COPMI and that it is possible to strengthen these factors with interventions [1, 2]. A recent RCT study has shown that support groups for COPMI aged 8 to 12 years are effective [11]. Children who participated in an intervention group sought more social support, had less unrealistic thoughts, and showed more perceived competence compared to children in the control group. Besides, these children perceived the support group as very useful, since they could share their experiences with peers.

A recommendation from the RCT study about support groups for COPMI was to further improve the involvement of parents [12]. Earlier studies showed that parental involvement is one of the most important factors in making a program for children effective [13, 14].

In addition to the interventions for COPMI, interventions for parents with a mental illness, such as an online educational program for parents with a mental illness having children with average intelligence, are being developed. It might be difficult for parents with a mental illness to join ‘live’ support groups for parents for several reasons, such as shame, low level of energy, or transport difficulties. Hence, an online educational program seems to be a more accessible way to provide parents with a mental illness parenting support. Van der Zanden et al. showed in their study with a pre-post-test design that after participating in an online educational program, parenting competence increased and emotional and behavioural problems in children decreased in comparison with baseline level [15, 16].

This study aims to examine the effectiveness of an adapted program for COPMI with mild ID. The ‘You are okay’ program consists of a support group for children with mild ID and an online educational program for their parents with a mental illness. The support group for children is based on the existing evidence-based support group for COPMI with average intelligence, and it has been adapted to the particular needs of children with mild ID [11]. Important factors that need to be considered in the adaptation of the evidence-based support group include simplifying language, providing additional sessions on basic emotions, and using examples reflecting the children’s perceptions. The adaptations are made in collaboration with professionals who work with children with mild ID and their parents. In addition, interviews with children with mild ID have provided valuable information regarding the adaptation process. Children with mild ID benefit from repeated information, especially simple and direct verbal information supported with visual information, and because of their concrete level of thinking, examples from their daily lives should be present [17]. We tested the adapted program for children with mild ID in a pilot study, the results of which have contributed to the current program and showed that children with mild ID are able to understand and reflect on their parents’ mental illness.

Parallel to the support group for children, parents will be offered an online educational program, following the recommendations of Van Santvoort on involving parents [12]. The existing online educational program for parents has been adapted for parents with children having mild ID. Simplification of language and adaptation of examples and assignments (for example if children are in residential care) were needed when adapting the parents’ online educational program because many parents of children with mild ID have mild ID themselves. They also benefit from simple use of language and concrete situations in their daily lives.

In Additional file 2, the two different parts of the ‘You are okay’ program are described. Figure 1 shows the theoretical model underlying the program based on a cognitive behavioural model. The support group for children is expected to decrease risk factors and increase protective factors in children while the online educational program for parents is expected to decrease risk factors and increase protective factors in parents. The long-term expectation is that the support group for children will contribute to less emotional and behavioural problems in children while the online educational program for parents will have a direct effect on parents and an indirect effect on children.

**Fig. 1 Fig1:**
[figure not shown]
The theoretical model. This figure explains the theoretical model underlying the specialised program of ‘You are okay’

The aim of this study is to examine the effectiveness of the ‘You are okay’ program in increasing protective factors and decreasing risk factors in children and parents. The primary outcome measure is children’s perceived competence, which consists of COPMI-specific cognitions, self-esteem and global self-worth. Secondary outcome-measures are children and parents’ perceived social support, perceived parental competence, parental involvement with their child’s treatment, positive parenting behaviour, and children’s emotional and behavioural problems.

## Methods/Design

### Design

This study involves a quasi-experimental design with two conditions: an intervention group and a control group. Figure 2 shows the study design with the inclusion and exclusion criteria and the group allocation and the assessments at baseline, post-test and follow up.

**Fig. 2 Fig2:**
[figure not shown]
Study design. This figure illustrates the study design with the allocation, inclusion and exclusion criteria, and different assessments

### Participants

Participants will be 10–20 year old children being treated for mild ID and behavioural problems at specialised institutes in the Netherlands and their parents with a mental illness. This age group is chosen because it corresponds with the age of the children in these institutes. The participating institutes specialise in treating children with mild ID and behavioural problems and offer children both residential care and part time treatment, depending on the severity of the problems of the children and their families. The researchers asked the institutes to participate in this study because of their population of children with mild ID.

The selected children had to have reached some stability in their lives in order to be able to reflect on their parent’s mental illness. Hence, the children who have been treated for at least three months, have not been in a crisis, and have been stable enough to handle potential emotional responses to the program, as indicated by the treatment coordinator, will be included in the study. Children who are not able to participate in a support group because of, for example, severe emotional or behavioural problems, will be excluded. In addition, children will be excluded if parents do not give consent, e.g., parents disagree with the child discussing the parent’s illness with others.

Many different support groups for different age groups of COPMI with average intelligence have been developed all based on the same principles. In the program ‘You are okay’, the experimental groups will formed according to children’s age; thus, age-groups will be formed. In the support group manual, different methods of the same exercises are described to match the needs of the specific age groups.

Treatment coordinators and social workers will select children whose parents acknowledge that they have a diagnosed mental illness. If there is no official diagnosis of a mental illness, but it can be assumed based on the contact with the parent and the parent’s acknowledgement of a mental illness, the parents may also be included. The severity of the parental mental health problems will be measured at baseline. If children have little or no contact with their parents, their family guardian has to agree with their participation and acknowledge that one of the parents has a mental illness. Both parents will be invited to participate in the study to complete the assessments. If the child has no contact with one of the parents, only the involved parent will be invited to participate, even if this is the parent without a mental illness. The parent who will complete the assessments will also be invited to join the educational program for parents. In addition to biological parents, other caregivers can participate, for example, foster parents or stepparents. When children perceive these persons as important caregivers, they can fulfil similar roles as biological parents.

### Procedure

Treatment coordinators and social workers will screen children and parents to be included in the study. The aims of the study will be explained to parents by phone or during a face-to-face appointment. Children and parents (or family guardians when involved) who will agree to participate and sign the informed consent form will be included. After inclusion, allocation will take place. Interviewers will administer baseline assessment to children and parents.

Assessments in both intervention and control group will be administered orally with a standardized protocol. Participants will be assessed at baseline, post-test assessment and follow up. Interviewers will visit and administer the questionnaires to children. Parents will be visited by interviewers or will be asked to answer the questions by phone. Because both children and parents might show difficulties understanding written information, simple language will be used in the information letters. Assistance will be provided to help participants complete the forms, and the study will be explained to children and parents face-to-face, allowing participants to ask their questions directly. At the same time, the interviewer will be able to check whether they understand the information. Because of the individual assessment appointments, a low attrition rate is expected. Participants will receive a reward of 5 euros after completing all assessments.

The Medical Research Ethics Committee (Independent Review Board Nijmegen) approved the study’s protocol (NL49448.072.14). The study protocol is registered at the Dutch Trial Register (NTR4845).

### Allocation

Using a quasi-experimental design, each child and his or her parent will be assigned to a condition (experimental group or control group) based on matching. Because in practice it is not possible and appropriate to form support groups with children of different ages and from different locations, matching based on age, gender, type of setting (residential or part-time) and location will be used. Therefore, it will be possible to start support groups in different locations with children of different age groups and an equal distribution of both genders and type of treatment. An independent researcher will perform the allocation before baseline assessment takes place and will assure that the experimental and control group will match.

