### Assessments

Instruments will be adjusted to help children with mild ID complete the assessments, with the use of colours and emoticons corresponding the response options. According to the pilot study, the assessments are appropriate for children with mild ID.

The primary outcome will be children’s perceived competence, which consists of global self-worth, social acceptance, and COPMI-specific cognitions. It will be measured using the Dutch version of the Self Perception Profile for Adolescents (SPPA) [20, 21]. Children will complete two subscales: global self-worth and social acceptance. Each subscale contains five items measured on a four-point Likert scales. Different colours will be used to underline the response options. The reliability of this instrument is sufficient [20]. This instrument has been widely used by researchers in the field of intellectual disabilities [22].

Children’s perceived competence will also be measured using a short questionnaire on COPMI-specific cognitions developed by Van Santvoort [11]. The scale assesses whether a child experiences guilt, shame, and loneliness in relation to his/her parent with a mental illness. It contains three items measured on a five-point Likert scale, which together measure the COPMI-specific cognitions. The written response options are accompanied by emoticons. According to the study by Van Santvoort [11], these three items were moderate to highly correlated with each other.

Secondary outcomes will be children and parents’ perceived social support, perceived parental competence, parental involvement with their child’s treatment, positive parenting behaviour and children’s emotional and behavioural problems.

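### Non-random allocation comes before the baseline assessment, and nothing stated withholds the condition until baseline is complete

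*Protocol article*

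**What the plan says.** The order is stated in two places in the protocol article. Allocation: "An independent researcher will perform the allocation before baseline assessment takes place". Procedure: "After inclusion, allocation will take place. Interviewers will administer baseline assessment to children and parents". Consent comes before both steps: "Children and parents (or family guardians when involved) who will agree to participate and sign the informed consent form will be included".

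Assignment is not random: "each child and his or her parent will be assigned to a condition (experimental group or control group) based on matching". The matching variables are age, gender, type of setting and location.

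On measurement, Procedure says: "Assessments in both intervention and control group will be administered orally with a standardized protocol". For the primary outcome, Assessments says: "Children will complete two subscales: global self-worth and social acceptance". A short scale on guilt, shame and loneliness about the ill parent is added. On the comparator, the abstract says: "Children in the control group will receive care as usual, and their parents will have no extra offer".

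Statistical analysis lists baseline as one of three time points at which the groups are compared, adjusts for baseline differences in demographic variables, and plans an intention-to-treat analysis with multiple imputation.

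**The concern.** A baseline taken after allocation is protected only if nobody involved in it knows the result. Here the conditions cannot be disguised once disclosed: one arm has a support group and an online parent programme, the other has usual care. The answers concern self-worth, shame and loneliness, and are given aloud to an interviewer who also helps and checks understanding. Expectation, disappointment or interviewer influence could move them.

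Social workers are also exposed. They help select the children, may support parents through the online programme, and complete a questionnaire on the child's emotional and behavioural problems. Parental illness severity, a planned moderator, is measured at the same post-allocation visit.

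Two things are at stake. First, without randomisation the baseline comparison is the main empirical check that the arms are alike. If knowledge of the condition can affect it, a baseline difference cannot be separated into selection and reaction to allocation. Second, a child lost between allocation and baseline leaves imputation with little beyond background data.

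**Working it through.** **1. Is the order stated or inferred?** It is stated. Allocation puts the assignment before baseline, and Procedure gives consent, allocation, baseline. The two sections agree.

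**2. Does the matching need this order?** No. Age, gender, setting and location are all known at inclusion, and none comes from the questionnaires. Equally, none requires allocation to precede them.

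**3. Is the condition withheld until baseline?** Procedure, Allocation, Assessments and Statistical analysis contain no such statement. They also contain no statement that it is disclosed earlier.

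**4. What would a shift do?** Let knowledge of the condition shift one arm's reports by b SD at baseline and by c SD at a later assessment. Let β be the slope of the later score on the baseline score. None of these is in the article.

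- Bias in a change-from-baseline contrast: c − b.
- Bias in a baseline-adjusted contrast: c − βb.
- Shift at baseline only (c = 0), with b = 0.2 and β = 0.5 assumed: −0.20 SD and −(0.5 × 0.2) = −0.10 SD.
- Shift that persists unchanged (c = b = 0.2): 0.2 − 0.2 = 0 and 0.2 − 0.5 × 0.2 = +0.10 SD.

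So size and sign depend on b, c and β, and on a choice of contrast. The article names a multi-level path analysis but not the form in which baseline outcome scores enter it.

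**5. What would early loss do?** First the plan's own figures (Sample size: 54 for two groups, 80 for four, 90 after 10% attrition). For a group-by-time interaction with g groups and m = 3 measurements, λ = f²·N·m/(1 − ρ), df1 = (g − 1)(m − 1), df2 = (N − g)(m − 1), two-sided alpha 0.05, power 0.80. With f = 0.175 and ρ = 0.5 (both assumed; the article says only that the effect is small to medium) this gives N = 54 and N = 80. Then 80/0.9 = 88.9, so 89, against 90 stated. The sample size is not in error on this point.

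The article gives no rate of loss between allocation and baseline. Illustration, with extra loss on top of the 10%:

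| Extra loss (assumed) | N remaining | Four-group power | Two-group power |
|---|---|---|---|
| 0% | 90 × 0.9 = 81.0 | 0.82 | 0.94 |
| 5% | 90 × 0.95 × 0.9 = 77.0 | 0.80 | 0.93 |
| 10% | 90 × 0.90 × 0.9 = 72.9 | 0.77 | 0.91 |
| 20% | 90 × 0.80 × 0.9 = 64.8 | 0.71 | 0.87 |

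Under these assumptions the two-group comparison keeps adequate power. The greater worry is loss that depends on the condition, which this table does not measure.

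**The case against.** The strongest reply is that allocating and disclosing are separate steps. A reader might infer that the condition is known at baseline; the article does not say so. The timing of disclosure and the masking of interviewers are details that a condensed article may leave to the full protocol. This stands, and it limits the point to a risk. It does not remove the point, because the order itself is stated twice and is what creates the need for concealment.

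A reader might also want to express the bias as a share of the expected effect. The documents do not support that: the shift, the slope and the numerical effect size would all be assumed, and a reporting tendency that persists after baseline would partly or wholly cancel from a change score.

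A reader might say that early withdrawal breaks matched pairs. The article describes balance between the groups and does not state one-to-one pairs. Consent comes before allocation, so only later withdrawal can depend on the condition. Individual visits, the 10% allowance and multiple imputation all mitigate loss, though imputation does little for a child with no questionnaires.

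Finally, a reader might conclude that baseline self-worth should be a matching variable. The article gives no correlation to show its value. Where assignment is not random, letting the allocator see outcome scores removes a safeguard that the present order provides. That safeguard is worth keeping.

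**Conclusion.** The point holds as a risk in the stated procedure. Non-random allocation precedes a self-reported, interviewer-administered baseline, the conditions are recognisable once known, and no concealment until baseline is described. Baseline scores may be influenced by the condition, and children lost before baseline would be in the intention-to-treat set without questionnaire data.

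The facts about order, conditions and outcome come from the text. That anyone learns the condition before baseline is an inference. The size and direction of any bias cannot be derived from the document, and the figures in the working are illustrations only. Severity is moderate: the change is cheap, and a baseline affected by knowledge of the condition could not be reliably repaired in the analysis.

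**What to change.** Preferred: reword Procedure and Allocation so that the order is consent, baseline assessment of child and parents, allocation by the independent researcher, then disclosure. Keep the four existing matching variables, and state that the allocator does not see baseline outcome scores.

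Minimum: keep the present order, but state that the allocation is withheld from children, parents, social workers and interviewers until that child's and parents' baseline assessments are complete.

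The cost is revised wording and, under the preferred order, a wait at each location until its baseline visits are done, so the earliest baselines there will be somewhat older when sessions start. The wait should be short, but the article gives no recruitment timetable from which to calculate it. The matching needs no new data.
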